## Patient Follow up: Management of Complications

1. If the neuritis / type 1 reaction worsens (as per defined criteria of VMT and sensory testing) while the steroid is being tapered, then the dose of Prednisolone will be STEPPED UP to the preceding dose. After 20 weeks when Prednisolone has been stopped, if worsening occurs, the patient will be restarted at 40 mg of Prednisolone.
2. If the patient develops medical complications like leucopenia, jaundice or anemia it is imperative that this is investigated as per the protocol to determine the etiology. It should not be assumed that complications are caused by the trial drugs.
3. In case the patient is detected to have potential adverse effects of the drug(s) by lab investigations as listed in the flow diagram, then code will be broken by study coordinator
4. In case the patient develops clinical symptoms and signs suggestive of a severe adverse effect, such as systemic sepsis or gastro intestinal bleed then the patient will be admitted into the corresponding hospital and treated accordingly. The Study Coordinator will be contacted and the case reviewed. The Study coordinator will determine whether to break the code or continue the trial after symptomatic treatment.
5. In case a patient gets pregnant while enrolled in the study, she can be reassured that Azathioprine is highly unlikely to affect the fetus and continued in the study. However she may discontinue if she so wishes, in which case her nerve function assessments will be continued as per schedule.
6. In case of infections such as Tuberculosis, patient will be started on Anti Tuberculosis Treatment (ATT) after relevant investigations and continued in the study.

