Treatment with corticosteroids improves both reactional skin lesions and neuritis. A retrospective study reported only a 50% improvement in clinical signs and symptoms of reactions involving nerves13, while other studies have reported improvement in nerve function of 60% to 70%.14 However upto 30% of patients with type 1 reactions or nerve function impairment may not improve with prednisolone.15

Patients treated with the standardized steroid course often require additional steroids while the dose is tapered – a recent trial conducted in Nepal showed 50% of patients treated with a 12 week prednisolone regimen required further steroids.16 The need for additional steroids prolongs the duration of steroid treatment and the total amount of steroid used. Another problem with using corticosteroids is the associated adverse effects.8 Concerns over such adverse effects of steroids used under field conditions have lead to pressure to keep the dose and duration to a minimum.17

The risks of adverse effects with standardized regimens of corticosteroids for the treatment of leprosy reaction in the field have been described.18

The adverse effects associated with corticosteroid therapy can be classified into minor such as moon face, fungal infections, acne and gastric pain. The major adverse effects being gastric ulcer, glaucoma, diabetes, hypertension, osteoporosis, cataract and a range of psychiatric disturbances ranging from mood alterations to psychosis. Besides these life-threatening infections can also occur. The risk of minor adverse effects while being on prednisolone was 16 % and 2% for major side effects. Dermatological side effects namely moon face, acne and fungal infections were seen in 6.5 % of patients on prednisolone .19

There is an urgent need for an adjunct to steroids in the treatment of type I reactions because:

1. 30-50% of patient with acute neuritis do not show neurological improvement when treated with the standard steroid regimens.
2. There is flare-up of skin lesions while steroid doses are tapered down.
3. Some patients require prolonged courses of steroids and become steroid-dependent.
4. Alternative treatments are needed for patients with contraindications to corticosteroids
5. Alternative treatments are needed for patients with severe neuritis who do not improve on steroid treatment.

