#### Inclusion Criteria:

Patients with acute (< 6 months) neuritis with or without accompanying type 1 reaction or recurrent reactional skin lesions without neuritis.

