## Patient outcome measures

### Primary outcomes

1. **Recovery of nerve function**

- Absolute improvement in nerve function as measured by Voluntary Muscle testing (one point improvement in VMT score) and Sensory testing (two point improvement in ST score) using standard methods as defined in the field manual.

1. **Recurrence of neuritis during or after treatment**

- Recurrence of neuritis is defined as a new nerve function impairment presenting in the form of a decrease in VMT score by one point and an ST score by more than 2 points either during the study period or during the follow up period and present for two consecutive testings.

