### *Definitions:*

### *Neuritis*: A leprosy patient is diagnosed as having neuritis when he/she has any of the following:

- Spontaneous nerve pain, paraesthesia or tenderness (or)
- New sensory or motor impairment of recent onset detected by voluntary muscle testing and sensory testing (or)
- Mixed sensory and motor signs

*Acute Neuritis*: For neuritis to be acute it has to have appeared within the last six months (defined either by previous testing or patients history of new sensory or motor loss)

*Type1Reaction* (T1R) is defined as the development of an acute or subacute inflammation affecting the skin and / or nerves occurring in leprosy, due to a hypersensitivity to *M.leprae* antigens, resulting in a change in the appearance of skin lesions and / or nerve damage and disability.

A T1R is diagnosed when a patient has erythema and edema of skin lesions. There may be accompanying neuritis and edema of the hands, feet and face. The skin signs are obligatory; the nerve and general signs optional.

*Acute T1R* is defined as the presence of erythematous and raised skin lesions with or without evidence of neuritis of less than 6 months duration prior to presentation.

*Recurrent reactional skin lesions* are defined as newly erythematous lesions that have either developed off steroids or whilst on steroids.

*Silent Neuropathy (SN)*

A patient is defined as having silent neuropathy when he/she has sensory and/or motor impairment of recent onset (< 6 months duration) in an area innervated by one or more nerve without signs of a reaction (RR or ENL) or nerve pain and with or without tenderness.

*Sensory Impairment:* A patient is diagnosed as having sensory impairment in any of the following situations: the monofilament threshold was increased from the normal threshold (2gm/purple for the hand and 10gm/orange for the foot) by three or more levels (filaments) on any site, OR two levels on one site AND at least one level on another site, or one level on three or more sites for one nerve.

*Motor Impairment:* A patient will be diagnosed as having motor impairment if the VMT score for any muscle is four or less on the 0-5 (modified) MRC scale.

*Worsening of skin lesions:* is defined as occurrence of a fresh episode of acute skin inflammation with or without edema while enrolled in the study.

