*Worsening of Acute Neuritis*: is defined as evidence of nerve function impairment as evidenced by at least a single point decrease in VMT score or a two-point decrease in ST score from baseline, in two consecutive testings.

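### The steroid step-up rule counts nerve worsening from the entry score, so a relapse that only gives back an earlier gain does not trigger it; for skin flares the protocol is inconsistent

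*Protocol*

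**What the plan says.** **Step-up rule.** Protocol, Patient Follow up: Management of Complications, item 1, returns prednisolone to the preceding dose if neuritis or type 1 reaction "worsens (as per defined criteria of VMT and sensory testing) while the steroid is being tapered". The next sentence restarts prednisolone at 40 mg if worsening occurs after week 20. It does not repeat the nerve-test qualifier.

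**Nerve worsening.** Under Definitions, worsening of acute neuritis is "at least a single point decrease in VMT score or a two-point decrease in ST score from baseline, in two consecutive testings". No other VMT or ST definition of worsening appears in the protocol. The recruitment flow chart places the baseline sensory and muscle tests at entry (Forms 4.0 and 5.0).

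**Skin worsening.** This is defined separately as "occurrence of a fresh episode of acute skin inflammation with or without edema while enrolled in the study". Item 1 does not refer to it. The Inclusion Criteria admit patients with "recurrent reactional skin lesions without neuritis". The Definitions make skin signs obligatory for a type 1 reaction and nerve signs optional.

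**Flow chart.** Its follow-up part has boxes for worsening and for adding steroids, with no nerve-test limit on either.

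**Recurrence.** The second primary outcome requires "a decrease in VMT score by one point and an ST score by more than 2 points" on two consecutive testings, with no reference value stated.

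**The concern.** A patient can respond to treatment, lose the whole response during the taper and still not meet the criterion for more steroid. Such patients may be common. The Background says that "30-50% of patient with acute neuritis do not show neurological improvement when treated with the standard steroid regimens", which implies that 50% to 70% do improve and could later give back a gain. It also warns that nerve damage may become irreversible without early and adequate treatment, and it gives as a reason for the trial that "There is flare-up of skin lesions while steroid doses are tapered down".

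There is a statistical consequence too. Objective 3 equates recurrence with needing further steroid, and the Statistical analysis section plans to explore additional steroid requirement. If the trigger is harder to reach after better recovery, an arm that recovers more may show fewer step-ups at the same rate and depth of relapse. Blinding does not remove this, because the asymmetry lies in the rule.

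**Working it through.** **Inputs.** The trigger comes from item 1 read with the definition of worsening of acute neuritis. The VMT scale comes from the definition of motor impairment, which applies "if the VMT score for any muscle is four or less on the 0-5 (modified) MRC scale". Baseline is taken as the entry test, and the words from baseline are taken to govern both the VMT and the ST fall. The protocol gives no figure for this rule, so there is none to reproduce.

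**Fall needed after a gain.** The rule fires if current VMT ≤ entry − 1 or current ST ≤ entry − 2, on two consecutive testings. After a gain of g VMT points or h ST points:

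- VMT fall needed = g + 1, that is 1, 2 and 3 points for g = 0, 1 and 2.
- ST fall needed = h + 2, that is 2 points for h = 0 and 4 for h = 2.

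A patient who just meets the recovery outcome (VMT +1, ST +2) can lose all of it without triggering, because the return is to entry and not below it.

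**Example.** Entry VMT 3, recovery to 5, then 3 on two testings. Fall from the recovered value: 5 − 3 = 2. Fall from entry: 3 − 3 = 0. The muscle meets the definition of motor impairment but not that of worsening. If it fell to 2 on two testings, the fall from entry would be 1 and the rule would fire.

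**All patterns for one muscle.** Entry b runs from 0 to 4, recovered value p from b + 1 to 5, and later value v from 0 to p − 1. The rule fires when v ≤ b − 1.

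| Entry b | Patterns | Fire | Missed |
|---|---|---|---|
| 0 | 15 | 0 | 15 |
| 1 | 14 | 4 | 10 |
| 2 | 12 | 6 | 6 |
| 3 | 9 | 6 | 3 |
| 4 | 5 | 4 | 1 |
| Total | 55 | 20 | 35 |

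Leaving out entry 0, 20 of 40 are missed. Of the 15 patterns with a fall of exactly one point, none fires. These are equally weighted patterns, not patient frequencies. They concern one muscle; a fall in ST or in another nerve could still trigger in the same patient.

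**Agreement with the recurrence outcome.** Take a patient at VMT +2 and ST +4 relative to entry who falls to +1 and +1. The falls are 2 − 1 = 1 and 4 − 1 = 3. Counted from the recovered value, this is a recurrence (VMT down by 1, ST down by more than 2). Under the worsening definition the patient is still above entry on both tests, so no step-up follows. Counted from entry, it is neither. The protocol does not say which applies to recurrence.

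**Skin flares.** A flare with unchanged VMT and ST meets the skin-worsening definition but not the nerve-test qualifier in item 1. After week 20, the unqualified sentence in the same item could cover it.

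**The case against.** The strongest reply has five parts.

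1. Item 1 says when the dose will be raised and does not forbid raising it otherwise. The medical officer judges improvement or worsening at every visit. This stands: a reader might infer that steroid is certainly withheld after a relapse, but the text shows only that the stated criterion is not met.

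2. A reader might infer that the rule never fires for a nerve that improved and then relapsed. It does fire once the fall passes the entry score by the threshold, as in 20 of the 55 patterns.

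3. A reader might infer that skin-only patients are denied step-up. A sympathetic reading attaches the nerve tests to neuritis and the skin definition to type 1 reaction. The post-week-20 sentence and the flow chart point the same way, although the chart's arrows are not visible in the text at hand. What remains is an inconsistency that four centres could resolve differently.

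4. Item 1 does not cite the definition by name, and the field manual, which is not shown, may hold further criteria. This limits certainty, but nothing shown overrides the protocol's own definition.

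5. An entry anchor with confirmation is a recognisable cautious choice, and the Background notes pressure to limit steroid. Additional steroid is neither a listed primary nor a listed secondary outcome. Both are true, and they bear on weight. They do not explain why the fall required should grow with earlier recovery.

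**Conclusion.** The point holds in limited form and should be fixed, because it concerns a dosing rule that the protocol itself sets. As written, the rule does not fire when a nerve improves and then relapses but stays less than 1 VMT point and less than 2 ST points below its entry score, even if the whole gain is lost. For skin flares the protocol is inconsistent; it does not plainly deny treatment.

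The size on the nerve side is the extra fall required, equal to the earlier gain. The effect on the additional-steroid comparison has a clear direction if one arm recovers more, but no magnitude can be given: the protocol does not report the distribution of gains, the depth of relapses or the share of skin-only patients. A reader might infer a quantified bias between arms, and the documents do not support one.

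The conclusion assumes that baseline means the entry tests, that it applies to both VMT and ST, and that the field manual does not set a different reference.

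**What to change.** Three short edits:

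- **Definitions, worsening of acute neuritis:** count a fall of at least 1 VMT point or 2 ST points from the highest value held at two consecutive testings since entry (the entry value if none is higher), confirmed at two consecutive testings.
- **Management of Complications, item 1:** after the nerve-test criteria, add: or worsening of skin lesions as defined.
- **Primary outcomes, recurrence of neuritis:** state the same reference value.

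The fall needed is then 1 VMT or 2 ST points whatever the earlier confirmed gain. All 55 patterns above would trigger, provided that both the gain and the fall are confirmed. Requiring the gain to be held twice stops a single high reading from raising the bar through test variability; the price is that a gain seen only once is still not protected.

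The cost is somewhat more step-ups, and so more steroid exposure, plus a reference value carried forward on the VMT and ST forms. No additional patients are needed.

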## Patient follow-up procedure

Patients will be followed up from trial entry until the end of the study. Follow up is composed of several elements. A follow up schedule is summarized in the flow chart.

1. At baseline the patient will have laboratory investigations. This will comprise Smear Bacteriological and Morphological Indices (Smear BI and MI); a complete blood count (Hb%, Total Leucocyte Count and Total Platelet Count); Serum Creatinine; Serum AST and ALT.
2. Patients will be followed up fortnightly for the first 8 weeks and then at 4 week intervals with a full blood count and liver function tests done at each visit
3. At each follow up visit a physiotherapist will review the patient nerve function (voluntary muscle test (VMT) and sensory testing (ST) assessment and record the details in specially designed forms. in **FORM 4.1 (**each subsequent visit is indicated as **4.2 to 4.14**) and **FORM** **5.1** to **5.14** (corresponding to the visit number).
4. The PI / study MO will review the patient during follow up visit and evaluate for improvement / worsening of the neuritis. They will record evidence of any primary or secondary end points and compliance with the medication, specifically looking for adverse effects of the drugs. This will be recorded in **FORMs 3.1** to **3.14.**
5. Any participant who has not returned back for a follow up for more than 2 weeks will be contacted at his / her home by phone or personal visit. And attempt will be made to bring them back to the hospital for assessment. A patient who returns to the clinic within 4 weeks of the last visit will be continued in the study and those who do not return within 4 weeks will be removed as dropped out from the study
6. After 20 weeks if a patient wishes to go out of station he/she maybe given 8 weeks of treatment at one point of time and a single follow-up session maybe missed. If two follow-ups are missed concurrently the patient will be treated as per routine clinical practices but will have to be removed from the study.
7. Any patient who has missed their treatment for 4 weeks concurrently will be removed from the study and will be treated as per routine clinical practices.
8. The records of the patients will be flagged in the TLM Patient information systems, to ensure that the study team is informed of any deaths that occur at home. The MO should visit the family to establish the cause of death

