## Criteria for breaking the code

| Laboratory Parameter | Cut-off Point |
| --- | --- |
| Hb | < 7 g % |
| TLC | < 3000 |
| Platelet Count | < 1 lakhs |
| SGOT | > 50 |
| Creatinine | > 2 |

In case of abnormal blood counts, the following guidelines should be followed:

| Laboratory Parameter | Level | Action |
| --- | --- | --- |
| Total WBC | < 3 X 109/l | Break Code / Continue steroids |
| Absolute Neutrophil Count | < 1.0 X 109 /l | Break Code / Continue steroids |
| Absolute Neutrophil Count | < 0.5 X 109 /l | **If febrile**, start **antibiotic** and look for source of infection  As per guidelines in Field Manual |
| Hb | < 7.0 g/dl | Break Code / Continue steroids |
| Hb | Fall > 3 g/dl from baseline | **Break Code / Continue steroids** |
| Platelets | < 100000 | **Break Code/ Continue steroids** |
| Serum Creatinine | > 50 % above baseline | **Break Code / Continue steroids** |
| SGOT | > 2 X upper limit of normal | **Break Code / Continue steroids** |

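### The code-break trigger list that the protocol points the coordinator to omits the neutrophil limit (and the haemoglobin-fall limit) that its own guideline table sets

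*Protocol*

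**What the plan says.** Three places in the protocol list laboratory triggers for breaking the code.

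- **The instruction.** Patient Follow up: Management of Complications, item 3, says that for potential adverse drug effects detected "by lab investigations as listed in the flow diagram, then code will be broken by study coordinator". The only flow diagram is the Flow Chart for Recruitment. On blood counts, its follow-up part lists Hb below 7.0, TLC below 3000 and platelets below 1 lakh next to the code-break box. It also shows SGOT below 50 and creatinine below 2.0 as normal. It has no ANC limit.
- **First table under Criteria for breaking the code.** It has five rows: Hb, TLC, platelets, SGOT and creatinine. None is ANC.
- **Second table under the same heading.** It is introduced by "In case of abnormal blood counts, the following guidelines should be followed" and contains the row "Absolute Neutrophil Count | < 1.0 X 109 /l | Break Code / Continue steroids". For haemoglobin it adds a code break on "Fall > 3 g/dl from baseline". A further row, for ANC below 0.5 x 10^9/l, gives an action for febrile patients and ends "As per guidelines in Field Manual".

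On testing, Patient follow-up procedure, item 1, itemises the baseline count as "a complete blood count (Hb%, Total Leucocyte Count and Total Platelet Count". Item 2 schedules follow-up visits "with a full blood count and liver function tests done at each visit" and does not list what the count contains.

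**The concern.** The Background section states that azathioprine causes significant bone marrow suppression. Three of the four arms receive it, for 24, 36 or 48 weeks, with prednisolone over the first 20 weeks. Neutropenia is therefore an expected toxicity, and the ANC row allows action before infection appears.

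The list that item 3 names does not contain that row. Someone who follows item 3 and the flow chart would not break the code for a patient whose neutrophils are below 1.0 x 10^9/l while the total leucocyte count is still 3000 or more. Someone who follows the second table would. Four hospitals report to one study coordinator in a double-blind trial, so the trigger should be the same wherever a reader looks: a missed code break costs safety, and an inconsistent one costs blinding.

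The second worry is practical. An ANC needs a differential count, and no listed test names one.

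**Working it through.** No sample-size or error-rate figure is involved. The check compares the lists and adds some simple arithmetic.

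**1. Where the lists agree.** TLC below 3000 per microlitre is the same as WBC below 3 x 10^9/l, so all three lists agree on total white cells. They also agree on Hb below 7 and on platelets below 100,000 (1 lakh).

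**2. Where they part on blood counts.**

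| Trigger | Flow chart (named by item 3) | First table | Second table |
|---|---|---|---|
| Total white cells < 3.0 x 10^9/l | yes | yes | yes |
| Hb < 7 g/dl | yes | yes | yes |
| Platelets < 100,000 | yes | yes | yes |
| ANC < 1.0 x 10^9/l | absent | absent | break code |
| Hb fall > 3 g/dl | absent | absent | break code |

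**3. Which patients fall in the ANC gap.** ANC = total leucocytes x neutrophil fraction. With ANC below 1.0 x 10^9/l, the neutrophil share is below:

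- at a total of 3.0: 1.0 / 3.0 = 33%
- at a total of 4.0: 1.0 / 4.0 = 25%
- at a total of 5.0: 1.0 / 5.0 = 20%

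None of these patients has a total below 3.0, so none meets the flow chart or the first table on white cells. The same holds for ANC below 0.5. That row gives an antibiotic action but no code break of its own, so unblinding there also depends on the ANC < 1.0 row being applied.

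**4. The haemoglobin fall.** A drop from 12.0 to 8.9 g/dl is 12.0 - 8.9 = 3.1 g/dl. It meets the second table, but 8.9 is not below 7.

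**5. Whether other provisions close the gap.** Item 2 of the complications section says "If the patient develops medical complications like leucopenia, jaundice or anemia it is imperative that this is investigated as per the protocol", but it gives no cut-off and does not mention the code. Item 4 covers clinical events such as sepsis, when the patient is already ill, and leaves the code to the coordinator's judgement.

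**6. Number of follow-up counts.** Fortnightly for 8 weeks gives weeks 2, 4, 6 and 8 = 4 visits. Four-weekly from week 12 to week 48 gives 10. The total is 14, which matches the follow-up forms numbered to 14. At full attendance this is 14 x 312 = 4,368 counts in the trial. Counts taken during azathioprine, at 78 patients per arm, are 78 x (8 + 11 + 14) = 78 x 33 = 2,574. These are numbers of tests, not of patients affected.

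**The case against.** The best reply is that nothing here contradicts anything else. Item 3 gives a sufficient condition for breaking the code and never says that only the flow diagram counts. The second table sits under the heading for code-break criteria, is worded as a directive, and is the more specific text on blood counts. Read together, the two texts break the code at ANC below 1.0. This largely stands. A reader might infer that the protocol sets two rival ANC limits, or that it tells sites to keep the blind at such a count. It does neither: one ANC limit is stated, and the other lists are silent. What remains is that item 3 does not say the second table supplements the diagram, and it names the diagram alone.

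A reader might also infer that no differential is done, so that the rule cannot work. The documents do not show that. The list without a differential is for baseline; the follow-up count is not itemised, and the field manual and Form 6.1, which are not shown, may settle it. The supportable statement is that the input may be missing.

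The flow chart survives only as loose text without its arrows, so the link from each box to the code break is inferred. The first table carries the same parameters without ANC, which removes most of that doubt.

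Safeguards do limit the consequence: a total count below 3000 breaks the code in every list, leucopenia must be investigated, clinical sepsis leads to admission and review, and the safety committee receives updates every six months. None of them is an ANC trigger.

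Finally, the two tables differ more directly on SGOT (above 50 against above twice the upper limit of normal) and on creatinine (above 2 against more than 50% above baseline). That is true, but those conflicts are separate and settling them would not close this gap.

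**Conclusion.** The point holds as a failure to align the triggers. The ANC limit and the haemoglobin-fall limit stand in the second criteria table and are missing from the list that item 3 names and from the first table. The practical gap for neutrophils is a patient with ANC below 1.0 x 10^9/l and total leucocytes of 3000 or more. Whether the ANC is available at follow-up cannot be told from the protocol.

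The number of patients affected cannot be given. The Background quotes 3.8% for leucopenia, which is a different event and cannot stand in for a low ANC with a total count above the limit. The point bears on patient safety and on consistent unblinding; power and alpha are unaffected. The conclusion assumes that the flow chart's surviving text is complete and that the field manual and Form 6.1 do not already supply the missing link. It is a modest correction, worth making because the drug is toxic to marrow and the change is cheap.

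**What to change.** 1. In Management of Complications, item 3, refer to the Criteria for breaking the code as well as to the flow diagram. This also brings in the haemoglobin-fall row.
2. Add ANC below 1.0 x 10^9/l to the follow-up branch of the flow chart and to the first criteria table.
3. In Patient follow-up procedure, item 2, specify a full blood count with differential. The ANC limit is absolute, so no baseline differential is needed for it.

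**Cost.** If the follow-up count already includes a differential, the change is to wording only. If not, it adds at most 14 differentials per patient, or 4,368 for 312 patients, on blood already drawn and with no extra visit. All arms need it, because the allocation is blinded. A few more code breaks are possible.

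The SGOT and creatinine limits need their own decision. Until that is made, the new cross-reference in item 3 should not be taken to settle which of those limits applies.
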